199 intervention. Based on the results of the pilot study, we concluded that it was

200 worthwhile to evaluate the efficacy of CBT for OAB and decided to design this study.

201

202 2. Purpose

203 The purpose of this study is to establish CBT for OAB based on conventional  
 204 behavioral therapies and to evaluate its efficacy in women with moderate to severe  
 205 OAB in a randomized controlled trial.  
 206

207 3. Study design  
 208 Open-label, parallel-group, multicenter, 1:1 randomized controlled trial  
 209

210 4. Selection of participants  
 211 4.1. Institutions  
 212 Department of Urology, Kyoto University Hospital  
 213 Department of Urology, Kyoto City Hospital  
 214 Department of Urology, Asukai Hospital, Kyoto Civil Medical Federation Ichioka  
 215 Urology Clinic  
 216

217 4.2 Inclusion and exclusion criteria  
 218 Inclusion criteria:  
 219 (1) Women between 20-80-year-old;  
 220 (2) Participants not having undergone any OAB treatment for more than 6 weeks or  
 221 participants taking pharmacotherapy lasting more than 6 weeks for OAB;  
 222 (3) Participants diagnosed with OAB based on their OAB symptom score (OABSS)\* (a  
 223 total OABSS score  $\geq 3$ , with an urgency score  $\geq 2$ ), with the total score being higher than  
 224 6 (OABSS; 6 to 11 points indicate moderate severity, 12 to 15 points indicate moderate  
 225 severity) (1);  
 226 (4) An Eastern Cooperative Oncology Group (ECOG) Performance Status of Grade 0;  
 227 and  
 228 (5) Participants who are able to understand explanations and sign a written informed  
 229 consent.  
 230

231 \*Overactive Bladder Symptom Score (OABSS):  
 232 It is a symptom score for OAB developed in Japan and used worldwide for diagnosis  
 233 and severity assessment (1). A urinary urgency score (Question 3) of 2 or higher and a  
 234 total score of 3 or higher are considered a diagnosis of OAB. Regarding severity, a total  
 235 score of 5 or less is considered mild, a score of 6-11 moderate, and a score of 12 or  
 236 more severe.  
 237

238 Exclusion criteria

- 239 (1) Abnormalities around the bladder (e.g., bladder cancer, bladder calculus, interstitial  
240 cystitis, endometriosis);  
241 (2) Urinary tract infection;  
242 (3) Surgery for urinary incontinence;  
243 (4) Pregnancy;  
244 (5) Disability to understand Japanese;  
245 (6) Depression;  
246 (7) Dementia; and  
247 (8) Participants judged otherwise unsuitable for participation by the researchers.  
248

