 593 hallucinations/delirium, QT prolongation, ventricular tachycardia

594

595 Beta 3-adrenergic receptor agonist

596 Main side effects: constipation, dry mouth

597 Serious side effects: urinary retention, hypertension

598

599 11. Statistical consideration

600 11.1 Sample size and rationale

601 Assuming a significance level of 5% bilaterally, a power of 80%, a symptom score  
 602 difference between groups (OAB-q) of 10, and a standard deviation of 20, the sample  
 603 size is 128 patients in both groups. Assuming a dropout rate of 15%, the target number  
 604 of participants is 150 in both groups.

605

606 11.2. Analysis participants

607 As an intention-to-treat (ITT) analysis, all participants for whom allocation have been  
 608 initiated will be included in the analysis. Only patients who adhere to this protocol (Per  
 609 Protocol Set: PPS) will also be analyzed as a sensitivity analysis.

610 Definition of PPS: Participants who meet the following 4 criteria

611 (1) Patients have received all intervention treatments.

612 (2) Intervention interval is less than 3 weeks.

613 (3) Patients have not received additional medical treatment for OAB at other hospitals

614 (4) All measurement data are available.

615

616 11.3 Statistical analysis

617 11.3.1 Primary analysis

618 A mixed-effects model with repeated-measures (MMRM) will be used to analyze the  
 619 primary outcome, the HRQoL total score of OAB-q, under the assumption of missing at  
 620 random. Estimates of the least squares mean group difference, 95% confidence interval,  
 621 and p-value will be calculated as the result of group  $\times$  time point estimation with the  
 622 change from baseline to each measurement point as the objective variable, treatment

group, time point, OAB severity, interaction between treatment group and time point as fixed effects, study participants as variable effects, and baseline values as covariates. Week 13 is the assessment point for the primary analysis. A multiple-testing procedure will be used to control for the familywise type I error rate at a two-sided significance level of 0.05. If the primary analysis at week 13 shows statistical significance, testing of other assessment points of the primary outcome is to be performed in a hierarchical manner: week 9 and week 5.

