### 11.3.2 Secondary analyses

Secondary analyses will be performed to supplement the results of the primary analysis of the study and to further the discussion of the clinical question. The same statistical methods will be used for the secondary outcomes as for the primary outcome. For AEs, the number and rate of occurrence in each group will be calculated.

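### The primary MMRM gives baseline OAB-q one slope for weeks 5, 9 and 13; a baseline-by-time-point term would protect the week-13 contrast, at almost no cost, if that slope changes

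*Protocol*

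**What the plan says.** Protocol section 11.3.1 takes as outcome the "change from baseline to each measurement point as the objective variable, treatment" group, time point, OAB severity and the group-by-time-point interaction being the fixed effects. It then adds "study participants as variable effects, and baseline values as covariates". No other interaction is named. The analysis assumes data missing at random. Week 13 is the primary assessment point, and it also gates the tests at week 9 and week 5.

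Section 11.3.2 extends the approach: the same "methods will be used for the secondary outcomes as for the primary outcome".

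Section 3 describes the design as "Open-label, parallel-group, multicenter, 1:1 randomized controlled trial". Under section 5.4, controls receive CBT only after the study is complete.

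Section 11.1 sizes the trial on a 10-point difference and an SD of 20. It takes no credit for baseline adjustment and gives no correlation between baseline and follow-up scores.

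**The concern.** The listed model lets the treatment effect differ by visit but holds the effect of baseline constant. If the relation between baseline and follow-up score weakens over time, a single fitted slope is too steep at week 13. Two things could follow.

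- **Precision.** The misfit goes into the week-13 residual and widens the standard error.
- **Bias.** Likelihood estimation is valid under missing at random only if the mean model is right. If women leave according to their baseline score, and do so differently by arm, the arms still observed at week 13 differ in baseline. A wrong slope then corrects that difference by the wrong amount.

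Differential dropout is conceivable here because the trial is open-label and controls wait for CBT. For example, more impaired controls and less impaired CBT participants might be the ones to leave.

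**Working it through.** **Inputs from the protocol.** Two-sided 5%, power 80%, difference 10, SD 20, 15% dropout, 150 in total (11.1); 1:1 allocation (section 3); model terms, missing at random and week 13 as primary (11.3.1).

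**Assumed, not in the protocol.** SD 20 at baseline and every visit; slopes β of follow-up score on baseline at weeks 5/9/13 as tabulated; residual correlation between visits of 0.6 to 0.7. With change as outcome the slope is β − 1, so the constraint is the same.

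**Step 1: the plan's own figure.** The normal approximation gives 2 × (1.96 + 0.842)² × (20/10)² = 62.8, so 63 per arm. The t-test has power 79.5% at 63 per arm and 80.1% at 64, hence 128. Then 128/0.85 = 150.6, against 150 stated. The figure reproduces, and it does not depend on the baseline term.

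**Step 2: precision with complete data.** Let c be the fitted common slope and d = β13 − c.

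- *Unstructured covariance.* c = Σ w_k β_k, with weights w = 1′S⁻¹/(1′S⁻¹1), where S is the residual covariance including the misfit. The week-13 SE is √[(4/150) × 400 × (1 − β13²)] with the term and √[(4/150) × 400 × (1 − β13² + d²)] without it. For 0.70/0.55/0.40 and residual correlation 0.7, the weights are 0.74/0.24/0.03, so c = 0.657 and d = −0.257. The SEs are √(10.667 × 0.84) = 2.99 and √(10.667 × 0.906) = 3.11, a ratio of 1.038.
- *Random intercept (compound symmetry).* c is the plain mean of the slopes, 0.55. The pooled terms are mean(1 − β²) = 0.6825 and mean(d²) = (0.15² + 0 + 0.15²)/3 = 0.015. The ratio is √(0.6975/0.6825) = 1.011.

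| Assumed slopes, weeks 5/9/13 | SE ratio, unstructured | SE ratio, compound symmetry |
|---|---|---|
| 0.55/0.55/0.55 | 1.000 | 1.000 |
| 0.60/0.55/0.50 | 1.002–1.003 | 1.001 |
| 0.70/0.60/0.50 | 1.013–1.016 | 1.005 |
| 0.70/0.55/0.40 | 1.031–1.038 | 1.011 |
| 0.75/0.60/0.45 | 1.036–1.046 | 1.012 |
| 0.80/0.50/0.20 (extreme) | 1.16–1.20 | 1.04 |

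The ratio is the SE without the term divided by the SE with it. Simulations with 150 women, 15% random dropout and residual correlation 0.6 agree for 0.70/0.60/0.50 and 0.75/0.60/0.45. Unstructured gave 2.99 vs 2.94 (1.7%) and 3.16 vs 3.04 (4.0%). Compound symmetry gave 2.734 vs 2.716 (0.7%) and 2.735 vs 2.696 (1.4%).

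**Step 3: power at a 10-point effect, random dropout.** Without versus with the term, unstructured: 92% vs 92% (0.70/0.60/0.50), 87% vs 91% (0.75/0.60/0.45) and 85.5% vs 89.2% (0.70/0.55/0.40). All exceed 80%.

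**Step 4: bias.** The shift is approximately (β13 − c) × (CBT minus control difference in mean baseline among women still observed). It needs both factors to be non-zero. Simulated change in the week-13 estimate from leaving the term out (unstructured, about 14% lost per arm in the dropout settings):

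| Setting | 0.60/0.55/0.50 | 0.70/0.55/0.40 |
|---|---|---|
| No dropout | −0.01 | −0.04 |
| Baseline-dependent dropout, alike in both arms | 0.00 | −0.01 |
| Baseline-dependent dropout, opposite by arm | −0.43 | −1.43 |

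Monte Carlo error is 0.01 to 0.05. Compound symmetry gave −0.67 − (−0.26) = −0.41 and −1.09 − 0.10 = −1.19 in the last row. With equal slopes and the same opposite dropout, the change was only −0.29 − (−0.27) = −0.02. The extreme 0.80/0.50/0.20 case gave −2.89.

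A separate simulation, with slopes 0.70/0.60/0.50 and 0.75/0.60/0.45 and opposite dropout, gave mean errors of 1.01 vs 0.17 and 1.24 vs −0.01 points (without vs with the term). The sign depends on which women leave which arm.

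Under opposite dropout and no true effect, rejection without versus with the term was 7.5% vs 5.8% (0.70/0.55/0.40), and 6.6% vs 5.3% and 8.6% vs 5.3% in the separate simulation. A further run found 4.9% vs 4.9% and 7.2% vs 6.5%. Monte Carlo error is about 1 percentage point. With a true 10-point effect, 0.70/0.55/0.40 and the shift running against CBT, power was 75.5% vs 88.7%.

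**The case against.** The strongest reply is that this is an ordinary protocol-level MMRM description. Whether a covariate interacts with visit is often settled in the SAP, which is not at hand and may add the term. That stands as far as calling the omission an error: it is a common modelling choice and contradicts nothing. It does not remove the point, because section 11.3.1 itself lists the terms and names one interaction, so the common slope is the model as stated.

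Several stronger readings are tempting, and the document does not support them.

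- *The week-13 interval is certainly wider.* Only if the slopes differ. The protocol gives no correlations, and all three assessments fall after the CBT sessions, within eight weeks of each other. Equal slopes cost nothing.
- *The common slope is pulled towards week 5.* That needs an unstructured or otherwise heterogeneous covariance. Participants as random effects, taken literally, means compound symmetry. The common slope is then the plain average over visits when data are complete, and the loss is smaller.
- *The contrast is biased.* Randomisation protects it even with a wrong common slope, unless baseline-dependent dropout also differs by arm. The protocol shows no such dropout and has features that work against it: CBT for controls on completion (5.4), gift certificates at weeks 5, 9 and 13 in both arms (section 18), and continued assessment after treatment stops (9.2).
- *The trial is underpowered.* Not under random dropout. Power fell below 80% only in a constructed setting that combined diverging slopes with opposite dropout.

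**Conclusion.** The point holds in conditional form and is minor. As written, the model imposes one baseline slope on three visits. If the true slope declines plausibly, week 13 loses about 0 to 1.4% of SE under a random intercept, or 0 to 4.6% under an unstructured covariance. The sample size is unaffected. If dropout also depends on baseline in different ways by arm, the week-13 estimate can move by roughly 0.4 to 1.4 points, which is 4 to 14% of the 10-point target, within the plan's own missing-at-random assumption. Any inflation of the type I error is modest and not consistent across runs.

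All these sizes rest on assumed slopes, residual correlations and dropout patterns, none of which the protocol supplies. The shift also scales with the assumed strength of the baseline-dropout relation. The case for acting is the imbalance of costs: the extra term is nearly free if it is not needed.

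**What to change.** In section 11.3.1, add baseline OAB-q HRQoL total score by time point to the fixed effects, naming the baseline variable explicitly. If a common slope is intended, say so and give the reason.

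The cost is one line of text and two degrees of freedom (three visits less one). If the slopes are equal, the SE rises by at most about 0.5% (2.732 vs 2.719 in the least favourable equal-slope run; 2.723 vs 2.723 with random dropout). No new data or patients are needed, and fixing the term beforehand avoids a later choice made with results in view.

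Optional: OAB severity by time point (two further degrees of freedom), and the same form with each outcome's own baseline for continuous secondary outcomes under section 11.3.2. Neither was tested here, so neither is requested on the strength of these figures.

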### 11.3.2 Secondary analyses

Secondary analyses will be performed to supplement the results of the primary analysis of the study and to further the discussion of the clinical question. The same statistical methods will be used for the secondary outcomes as for the primary outcome. For AEs, the number and rate of occurrence in each group will be calculated.

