349  $21+22+23+24+25+26+27+28+29+30+31+32+33)]/125 * 100$   
350

351 Secondary outcomes:  
352 - OAB-q subscales other than HRQoL total scores (2)  
353 The subscales other than the HRQoL total score are calculated as follows.  
354 - Symptom bother:  $[(\text{Question score } 1+2+3+4+4+5+6+7+8)-8]/40 * 100$   
355 - Coping behaviors:  $[48 -(\text{question score } 9+11+16+21+22+26+32+33)]/40 * 100$   
356 - Concern/worry:  $[42 -(\text{question score } 12+13+14+19+23+25+29)]/35 * 100$   
357 - Sleep:  $[30 -(\text{question score } 10+15+17+24+30)]/25 * 100$   
358 - Social interaction:  $[30 -(\text{question score } 18+20+27+28+31)]/25 * 100$   
359 - Overactive bladder symptom score (OABSS)(1)  
360 This is a self-administered questionnaire symptom score for OAB developed in Japan  
361 and used for diagnosis and severity assessment. Regarding severity, a total score of 5 or  
362 less is judged as mild, 6-11 as moderate, and 12 or more as severe.  
363 - King Health Questionnaire (KHQ) (3)

364 A QoL self-administered questionnaire specific to urinary incontinence, consisting of 19  
 365 questions in 8 domains, which has also been validated for OAB.  
 366 - General health perception:  $[(Q1 \text{ score} - 1)/4 * 100]$   
 367 - Incontinence impact:  $[(Q2 \text{ score} - 1)/3 * 100]$   
 368 - Role limitations:  $[(Q3a+Q3b \text{ score} - 2)/6 * 100]$   
 369 - Physical limitations:  $[(Q4a+Q4b \text{ score} - 2)/6 * 100]$   
 370 - Social limitations:  $[(Q4c+Q4d+Q5c \text{ score} - 3)/9 * 100]$  when  $1 \leq Q5c$   
 371 When  $Q5c = 0$ ,  $[(Q4c+Q4d+Q5c \text{ score} - 2)/6 * 100]$   
 372 - Personal relationships: when  $2 \leq Q5a+Q5b$ ,  $[(Q5a+Q5b \text{ score} - 2)/6 * 100]$   
 373 When  $Q5a+Q5b = 1$ ,  $[(Q5a+Q5b \text{ score} - 1)/3 * 100]$   
 374 When  $Q5a+Q5b = 0$ , treat as missing values  
 375 - Emotions:  $[(\text{score of } Q6a+Q6b+Q6c - 3)/9 * 100]$   
 376 - Sleep/energy:  $[(Q7a+ Q7b \text{ score} - 2)/6 * 100]$   
 377 - Severity measures:  $[(Q8a+ Q8b+ Q8c+ Q8d+ Q8e \text{ score} - 5)/15 * 100]$   
 378 - Patient Global Impression-Improvement (PGI-I) (4)  
 379 A multi-item option to evaluate the general improvement score of symptoms using a  
 380 7-point Likert scale self-administered questionnaire, with 1 to 2 defined as improvement,  
 381 and a binary variable of with improvement and without improvement.  
 382 - Patient Global Impression-Severity (PGI-S) (4)  

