 383 It is a multiple-choice instrument that evaluates the overall improvement score of  
 384 symptoms using a 4-point Likert scale self-administered questionnaire. 1 to 2 is defined  
 385 as improvement, and is evaluated with and without improvement as a binary variable.  
 386 - EQ-5D-5L (5)  
 387 A 5-question scale measuring HRQoL with a self-administered questionnaire.  
 388 - Hospital Anxiety and Depression Scale (HADS) (6)  
 389 A 14-item self-administered questionnaire developed to assess anxiety and depression in  
 390 participants with physical symptoms. Anxiety and depression are calculated by  
 391 summing the scores from a point distribution table. Scores of 0-7 indicate no anxiety or  
 392 depression, scores of 8-10 are suspicious diagnoses, and scores of 11 or higher are  
 393 confirmed diagnoses.  
 394 - Frequency voiding chart (FVC)  
 395 The following information is entered in a self-administered form: waking time, sleeping  
 396 time, time of urination, amount of urination per time, frequency of urination, and  
 397 presence or absence of urinary incontinence with a sense of urgency. Of these, the  
 398 average number of urination, urinary incontinence, and urinary urgency frequency per  
 399 24 hours will be used as the evaluation items.

400 - Patient Satisfaction

401 A general improvement score of symptoms was used as a multiple choice to be

402 evaluated using a self-administered questionnaire with a 5-point Likert scale. 1 to 2 is

403 defined as satisfaction with treatment and is evaluated with a binary variable of satisfied

404 or not satisfied.

405 - Change in medication (change, addition, or discontinuation)

406 - Treatment compliance

407 The degree of compliance with the techniques used in each session is evaluated.

|     |           |                               |
|-----|-----------|-------------------------------|
| 408 | Session 1 | Self-monitoring               |
| 409 |           | Improvement of lifestyle      |
| 410 |           | Pelvic floor muscle exercises |
| 411 | Session 2 | Self-Monitoring               |
| 412 |           | Lifestyle modification        |
| 413 |           | Pelvic floor muscle exercises |
| 414 |           | Exposure                      |
| 415 | Session 3 | Self-Monitoring               |
| 416 |           | Improvement of lifestyle      |
| 417 |           | Pelvic floor muscle exercises |
| 418 |           | Exposure                      |

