| 419 | Session 4 | Self-Monitoring               |
| 420 |           | Improvement of lifestyle      |
| 421 |           | Pelvic floor muscle exercises |
| 422 |           | Exposure                      |

423 At the time of evaluation after the end of the intervention, the degree to which each

424 technique is performed (compliance) will be assessed.

425 - Dropout rate

426 The percentage of assigned participants who drop out during the study will be

427 calculated. There will be two types of dropouts in this study: intervention

428 discontinuation and evaluation discontinuation (see "9. Discontinuation Criteria" for

429 details).

430

431 6.3. Measurement methods

432 OAB-q, OABSS, KHQ, GIS, EQ-5D-5L, HADS, FVC, and treatment compliance

433 before the start of CBT, at Week 5 (after treatment ends), Week 9 (4 weeks after

434 treatment ends), and Week 13 (at the end of follow-up) of the paper or online-based

435 registration system (REDCap\*) Patients will be asked to complete a self-administered

436 questionnaire. Dropout rates and incidence of AEs will be confirmed by the therapist at  
437 each visit. Treatment feedback will be completed at the end of follow-up, either on  
438 paper or in a self-administered questionnaire in REDCap\*. The same will be done for  
439 the study at all sites, and data will be collected online with security assured.

440

441 \* REDCap is a data collection and management system developed by Vanderbilt  
442 University in the U.S. under the NIH Clinical Bridging Research Support Grant and  
443 distributed free of charge mainly to academia, and is used at 3090 facilities in 128  
444 countries around the world. In Japan, Osaka City University provides the system; on  
445 April 1, 2017, the Department of Clinical Statistics, Graduate School of Medicine,  
446 Kyoto University contracted with Osaka City University to begin research use of the  
447 system. Under this contract, the data server is dedicated to Kyoto University, which is  
448 contracted by Osaka City University, and its management is entrusted to Osaka City  
449 University. The data server is equipped with complex security measures. Access to the  
450 server and system is restricted by user accounts and passwords issued to individuals,  
451 and all audit trails are recorded.

452

453

454 **The schedule of this study.**

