## 514 8. Masking

515 Due to the nature of the intervention, this study cannot be masked to the  
516 therapist/participant. Statistical analysts will not be able to review the results until the  
517 end of the study. In addition, REDCap keeps a complete history, so the history can be  
518 traced for any evidence of confirmation of the results.

519 Masking: Statistical Analysts  
520 Not Masking: Participants, Therapists, Outcome adjudicators  
521

522 9. Discontinuation criteria

523 There will be two types of discontinuations from the study: intervention discontinuation  
524 and evaluation discontinuation.  
525

526 9.1. Deviation from protocol treatment

527 Any of the following will be considered a deviation from the protocol treatment. In such  
528 a case, the participant has not dropped out of the study, and periodic evaluation will be  
529 conducted unless the participant withdraws consent for evaluation.

530 (1) If the participant has never received any intervention treatment  
531 (2) When the intervention interval is more than 3 weeks.  
532 (3) When the participant has received additional treatment for OAB at another hospital.  
533 (4) When there are no valid data after the start of treatment.  
534

535 9.2. Discontinuation of intervention

536 If any of the following conditions apply, the protocol treatment will be discontinued at  
537 the discretion of the physician in charge of the study. In such cases, the participant is not  
538 dropped from the study, and subsequent periodic evaluations will be conducted unless  
539 the participant withdraws consent for the evaluation.

540 (1) When the participant wishes to discontinue the intervention  
541 (2) When a serious AE occurs and it is deemed difficult to continue the intervention  
542 (3) When the physician in charge of the study determines that the harm of continuing  
543 the intervention outweighs the benefit for some reason, although no serious AE has  
544 occurred  
545 (4) Other cases in which the investigator deems it inappropriate to continue the  
546 intervention.  
547

548 9.3. Discontinuation of valuation

549 If a study participant withdraws consent for a periodic evaluation, no further follow-up  
550 will be conducted.

551

552 10. Reporting of adverse events and ensuring the safety of study participants

553 10.1 Definition of adverse events

554 Adverse events (AEs) are any unwanted or unintended signs or symptoms that occur in

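### Section 11.3.2 extends the primary change-from-baseline MMRM to five secondary outcomes it does not suit, and section 6.2 mislabels PGI-S and dropout

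*Protocol*

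**What the plan says.** Section 11.3.1 fixes the primary method: "A mixed-effects model with repeated-measures (MMRM) will be used to analyze the" OAB-q HRQoL total score. The dependent variable is "change from baseline to each measurement point as the objective variable, treatment" group, time point, OAB severity and the group-by-time interaction are fixed effects, the participant is a random effect, and the baseline value is a covariate. The result is a least-squares mean difference at each time point.

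Section 11.3.2 then states: "The same statistical methods will be used for the secondary outcomes as for the primary outcome". The next sentence makes one exception: "For AEs, the number and rate of occurrence in each group will be calculated".

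Section 6.2 defines the secondary outcomes. PGI-I is a "7-point Likert scale self-administered questionnaire, with 1 to 2 defined as improvement", analysed as yes or no. PGI-S rates "symptoms using a 4-point Likert scale self-administered questionnaire. 1 to 2 is defined" as improvement, again as yes or no. Patient satisfaction is a 5-point item cut to satisfied or not. Change in medication is listed as a change, addition or discontinuation. Treatment compliance is the degree to which session techniques are carried out, and section 5.4 gives the control group no CBT during the study.

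For dropout, section 6.2 says that the percentage of assigned participants will be "calculated. There will be two types of dropouts in this study: intervention" discontinuation is one and evaluation discontinuation the other. Section 9.2 says that protocol treatment is stopped at "the discretion of the physician in charge of the study. In such cases, the participant is not" removed from the study, and that periodic evaluation goes on unless she withdraws consent to it.

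**The concern.** This is a stated rule, not a detail left open for a statistical analysis plan. It assigns one model to every secondary outcome except adverse events, and section 6.2 defines several of those outcomes in a form the model does not suit. An analysis plan would have to follow a rule that does not work for them or depart from the protocol.

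The trial is open-label and these outcomes are self-reported. PGI-I, PGI-S and satisfaction are results that readers tend to quote. If the prespecified method cannot sensibly be used, the model, time point and effect measure for these outcomes are in effect not fixed by the protocol.

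The two definitions add to this. A PGI-S score of 1 to 2 at a visit describes where a participant is, not whether she has changed. Dropout means different things in sections 6.2 and 9.2, so a reported rate could not be read without knowing which was used.

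**Working it through.** **Step 1. Sort the 13 secondary outcomes (section 0.6) by what the model needs:** a score that can be treated as continuous, a baseline value, repeated visits, and values in both arms.

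| Outcome | Form in section 6.2 | Fit to the section 11.3.1 model |
|---|---|---|
| OAB-q subscales, KHQ, OABSS, EQ-5D-5L, HADS, FVC (6) | scores or mean daily counts | fits |
| PGI-I | binary rating of improvement | no meaningful pre-treatment value |
| Patient satisfaction | binary, about treatment received | no meaningful pre-treatment value |
| PGI-S | binary | can be fitted, unsuitable |
| Change in medication | event | no baseline |
| Treatment compliance | use of CBT techniques | no values in controls |
| Dropout rate | percentage of those assigned | section 6.2 gives its own calculation |
| Adverse events | number and rate | exempted in section 11.3.2 |

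Check: 6 + 5 + 1 + 1 = 13. Five outcomes do not suit the rule. Leaving out adverse events, that is 5/12 = 42%. Leaving out dropout as well, it is 5/11 = 45%.

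**Step 2. What the model can estimate.** For weeks 5, 9 and 13 the fixed-effect design has 8 columns: intercept, group, two time terms, severity, baseline and two group-by-time terms. Its rank on a simulated design of 64 per arm was:

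- Full data: 8 of 8.
- Baseline absent or the same for everyone: 7 of 8. The baseline term is lost, and change from baseline has no content. This is the case of PGI-I.
- One time point and no baseline: 3 of 8. Intercept, group and severity remain. This is the case of an event recorded once per participant, such as medication change. It is also the case of satisfaction, if satisfaction is the treatment feedback that section 6.3 places at the end of follow-up.
- CBT arm only: 5 of 8. Group and both group-by-time terms are lost, so there is no between-arm contrast. This is the case of compliance.

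**Step 3. PGI-S.** With a 0/1 indicator, a participant at 1 at baseline can only change by 0 or -1, and one at 0 only by 0 or +1. The model runs, but the possible values depend on baseline, and the mean difference is not a natural summary of a yes/no outcome. Separately, a participant scoring 1 to 2 before treatment and unchanged at week 13 meets the section 6.2 definition of improvement.

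**Step 4. The schedule does not rescue the rule.** Section 6.3 lists GIS (apparently the two global impression items) and treatment compliance before CBT and at weeks 5, 9 and 13, and its schedule table marks secondary outcomes as a group at the same points. That gives PGI-S a real baseline. It does not give meaning to a pre-treatment rating of improvement or of compliance with techniques not yet taught.

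**Step 5. The primary outcome.** The sample size in section 11.1 does not depend on this point. For a difference of 10, SD 20, two-sided 5% and 80% power, the t-test solution is 63.77, so 64 per arm and 128 in total, as stated. With 15% dropout, 128/0.85 = 150.6, against the stated 150.

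**The case against.** The best defence is that these outcomes are supportive. Section 11.3.2 says so, and the testing hierarchy in section 11.3.1 covers only the OAB-q HRQoL total score at weeks 13, 9 and 5. Models for supportive binary outcomes are often left to the analysis plan, and a general sentence can be read sensibly. This stands as to weight: no confirmatory claim or error rate is affected. It does not remove the point, because the sentence makes a positive assignment and lists its one exception.

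It can also be said that section 6.2 only describes compliance as evaluated or assessed, with no between-group test. That is fair, but section 11.3.2 still covers it by its terms, and one clause would settle it.

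Three stronger readings are tempting and are not supported:

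- A reader might infer that the rule is impossible for half of the secondary outcomes. Dropout has its own percentage calculation in section 6.2, and a linear model on binary PGI-S with a baseline is unsuitable rather than impossible.
- A reader might infer that the dropout comparison is biased against CBT, because only that arm can stop an intervention. Section 6.2 names two types and refers to section 9, which defines them separately. Nothing says that they will be added together and compared between arms, and any size put on such a bias would rest on assumed rates alone.
- A reader might infer that the PGI-S definition biases the treatment contrast. Randomisation balances baseline PGI-S in expectation, and the primary model adjusts for baseline. The fault is in what the label claims.

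**Conclusion.** The point holds as a should-fix. Section 11.3.2 assigns a change-from-baseline MMRM to five outcomes that it does not suit: PGI-I, patient satisfaction, medication change and compliance, where it cannot be fitted meaningfully, and PGI-S, where it is a poor choice. Two definitions in section 6.2 are also faulty: improvement on a severity scale without reference to baseline, and dropout that includes participants whom section 9.2 keeps in the study.

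The primary analysis, its testing hierarchy and the sample size are unaffected. The conclusion rests on the protocol's own definitions. Two readings are assumptions: that GIS in section 6.3 means the PGI items, and that treatment feedback there includes satisfaction. If satisfaction were instead collected at each visit, it would still be binary and still lack a meaningful pre-treatment value.

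**What to change.** In section 11.3.2:

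- Limit the MMRM sentence to the continuous scores: OAB-q subscales, KHQ, OABSS, EQ-5D-5L, HADS and FVC.
- For PGI-I, PGI-S and satisfaction, name a binary-outcome method, for example logistic or modified Poisson regression at week 13, or GEE where the item is repeated. Report a risk difference with 95% CI, adjusted for at least OAB severity as in the primary model.
- Compare medication change as proportions, with a risk difference and CI.
- Describe treatment compliance in the CBT arm only.

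In section 6.2:

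- Define PGI-S improvement relative to baseline, or relabel a score of 1 to 2 as a severity status and adjust for baseline. The documents do not dictate a particular cut-off for change.
- Reconcile the dropout definition with section 9.2. Report the two types of discontinuation separately, and compare only evaluation discontinuation between arms.

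The cost is a short table in section 11.3.2 and two edits in section 6.2. No new data, visits or participants are needed.
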